### Phase V

This final phase will consist of analysis of pilot study data, incorporation of pilot findings into the refinement of the modified intervention, and preparation for future funding to develop a more rigorous evaluation of the intervention. A concurrent triangulation approach [57] will be used to integrate qualitative and quantitative data generated from this pilot. A set of questions will guide this data integration process to identify themes, patterns, and conflicts: What patterns emerge from each set of findings? Do they converge? If not, what are their discrepancies and what additional data and analysis are needed to understand these discrepancies? All study results will be presented and discussed with the CAB to inform next steps and future plans.

### Data analysis

Quantitative data entry and analysis will utilize SAS version 9.1.3 (SAS Institute, Inc., Cary, NC, USA). ATLAS.ti (ATLAS.ti Scientific Software Development GmBH, Berlin, Germany), a qualitative data management software [58], will be used to manage and analyze all qualitative data.

### Quantitative analysis

All tests will be two-sided and performed at significance level α = 0.05.

### Preliminary analyses

Preliminary analyses will consist of examining distributions of all baseline variables, identifying outliers, and calculating descriptive statistics. For longitudinal data, we will examine the distributions and calculate descriptive statistics for variables relevant to study aims at each time point. Proper transformation will be considered to meet assumptions of parametric models. Graphics will be used to explore bivariate associations, especially patterns over time for variables of interest.

### Accounting for missing data in the analysis

If a patient drops out of the study, we will record the stated reasons for dropout and make all efforts to obtain a final assessment. Failing this, the end-of-treatment assessment will be the patient's last scheduled assessment. The analysis of acceptability as measured by the Client Satisfaction Questionnaire (CSQ) will be based on a multilevel model with subject-specific random intercepts. For analyses that include missing outcomes, PROC MIXED in SAS allows for continuous data that may be missing for some patients due to lack of completion of assessments. Measurement at each time point on each patient contributes to the analysis. Thus, complete outcome information for all patients at all sessions is not needed. For analyses that include missing covariates, we will use multiple imputation to account for missing data. The inferences from incomplete data are valid, provided the missing data are missing at random [59]. Unfortunately, this assumption is untestable in most medical research. When we suspect this assumption does not hold, we will assume a model for the missing mechanism that depends on the unobserved outcome value and do the analysis incorporating the assumed model and conduct sensitivity analysis [60-62].

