### Phase IV

This phase will complete IM step 6 (evaluation) with a single group, pre-post, 12-month open pilot study (N = 30) carried out at WHCS. Two SW CMs will deliver the modified intervention, each carrying a caseload of 15 patients. Thirty adult Hispanic patients with SMI will be recruited. Inclusion and exclusion criteria are identical to those in phase IV. Based on the PCARE study recruitment rate of 69%, we will screen at least 45 patients to achieve our recruitment goal. A bilingual RA will recruit patients at WHCS through flyers, canvassing of waiting rooms, word of mouth, and provider referrals. We have allocated 18 months to this phase, which provides a six-month cushion for unanticipated problems with recruitment and attrition. Descriptions of the proposed measures for this study are presented in Table 3. As part of the planning process for this phase, the CAB will assess the appropriateness of these outcome measures for the intended patient population and, if necessary, identify other culturally relevant measures for key constructs (*e.g.*, acculturation, health literacy, illness perceptions).

**Table 3 T3:** Description of measures

Construct	Measure description
Feasibility	Study recruitment, assessment completion, and treatment attendance rates
Acceptability	CSQ and postintervention focus groups. The CSQ is an eight-item questionnaire scored on a four-point Likert-type scale. Scores range from 8 to 32, with higher score indicating higher satisfaction [68]. The CSQ is available in English and Spanish [69] and has excellent internal consistency in Hispanics [70].
Patient activation	PAM-13, [71] a 13-item scale that assesses patients' knowledge, skills, and confidence about self-management. Scores range from 0 (no activation) to 100 (high activation). PAM-13 has strong psychometric properties, including content and construct validity [71], has been tested across a range of chronic illnesses [72,73], and is available in English and Spanish.
Receipt of preventive primary care	PCARE study measure drawn from the USPSTF guidelines [74]. A total of 23 indicators are examined across four domains: (1) physical examinations, (2) screening tests, (3) vaccinations, and (4) education. Scored based on patients' medical records and self-report at baseline, three months, and six months. An aggregate preventive services score calculates the proportion of appropriate services obtained [18].

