Health and mental health-related quality of life	SF-12 [75], a self-report measure available in English and Spanish and validated among adults with SMI that generates two summary scores for physical and mental health-related quality of life [76]. Summary scores range from 0 to 100, with higher scores reflecting better health.
Covariates	Demographics: *e.g.*, race/ethnicity, age, gender, education, and marital status Acculturation: nativity, language dominance, time in the United States, age of migration; the Bidimensional Acculturation Scale [77], a 24-item self-report measure that uses separate four-point scales to tap acculturation-related changes in two languages. Barriers to medical care: a list of 11 common factors that may prevent patients from seeking medical care [78,79]. Comorbid medical conditions: a list of 17 common medical conditions by patient self-report.

CSQ = Client Satisfaction Questionnaire; PAM-13 = Patient Activation Measure; PCARE = primary care, access and referral; USPSTF = U.S. Preventive Services Task Force; SF-12 = Short Form Health Survey; SMI = serious mental illness.

The primary outcomes of the pilot study are feasibility and acceptability. Two post-intervention FGs will be conducted with study participants to explore their reactions to the intervention. Each FG will be composed of 8-10 patients and follow the FG methods described in phase II. Although this is not an efficacy trial, we would be remiss in not taking this opportunity to initially explore the intervention's effect, as measured by patient activation, receipt of preventive primary care, and physical- and mental-health-related quality of life. Covariates include demographics, acculturation, barriers to care, and comorbid medical conditions. The RA will assess patients at baseline, 6 months, and 12 months. Self-report measures and medical chart abstractions will be obtained. Patients will be asked for consent to access medical records at WHCS and their primary care clinic. The RA will conduct these abstractions under [name]'s supervision.

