### Precision analysis

Since this is a pilot study for a future large randomized trial, we did not conduct a power analysis in accordance with recommendations in the new National Institutes of Health guidelines http://grants.nih.gov/grants/guide/pa-files/PAR-09-173.html and Kraemer and Kupfer [63]. Instead, we conducted precision analysis for the main study outcomes--feasibility and acceptability--by computing margin of error of an estimated rate to assess the precision that can be achieved by the proposed sample size. Margin of error is half the width of a confidence interval of an estimator. The smaller the margin of error, the tighter the confidence interval and the more precision we achieve for an estimator. We used the original PCARE [18] study treatment and completion assessment rates to estimate standard errors and margins of errors. PCARE's observed treatment completion rate was 0.68, with a sample size of 30, the standard error was 0.085 and the margin of error was 0.167. PCARE's observed assessment completion was 0.78 at 6 months and 0.69 at 12 months, the corresponding standard error is 0.076 and 0.084, respectively, and the margin of error is 0.15 and 0.17, respectively. For the CSQ scores (acceptability measure), when the standard deviation of the improvement of CSQ is 1, 2, or 4 points, the corresponding margin of error for estimating mean improvement is 0.18, 0.36, and 0.72, respectively. In all, our precision analysis indicates we have small margin of errors for each of our main study outcomes.

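### The single dropout rule does not use the planned chart access to obtain leavers' record-based preventive-care data at the scheduled times

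*Protocol article*

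**What the plan says.** **Dropout rule** (Accounting for missing data in the analysis). When a patient leaves, the team will "record the stated reasons for dropout and make all efforts to obtain a final assessment". The fallback is: "Failing this, the end-of-treatment assessment will be the patient's last scheduled assessment". No distinction is made between interview outcomes and chart outcomes, or between stopping care-manager visits and leaving the study. The same section adds that "Measurement at each time point on each patient contributes to the analysis", and it plans sensitivity analysis when missing at random is doubted.

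**Source of the preventive-care outcome** (Phase IV, Table 3). "Scored based on patients' medical records and self-report at baseline, three months, and six months".

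**Record access and timing** (Phase IV text). "Patients will be asked for consent to access medical records at WHCS and their primary care clinic". The research assistant does the abstraction. On timing: "The RA will assess patients at baseline, 6 months, and 12 months".

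**Expected completion** (Precision analysis). "PCARE's observed assessment completion was 0.78 at 6 months and 0.69 at 12 months".

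**Analysis** (Exploratory analysis). Preventive-care rates are to be reported with confidence intervals. No model is named for this outcome.

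**The concern.** The rule suits outcomes that need the patient in the room, such as satisfaction, activation and quality of life. Preventive care is partly different: its record-based indicators can be read from the chart at the due date whether or not the patient attends. Under the stated rule, a leaver contributes one assessment at the time of leaving, or an earlier value relabelled as end-of-treatment. If 6 months is the first visit after baseline, a patient who leaves before then without a final assessment could have baseline stand as the endpoint. Services received afterwards, or their absence, would not enter that value.

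What is at stake is the usefulness of this estimate for planning the larger trial. Patients who leave may well differ from those who stay in their links to primary care. The plan would then rely on modelling, or on an out-of-date value, for something that could in part be looked up.

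**Working it through.** **Inputs.** From the article: N = 30, single group (Phase IV); assessment completion 0.78 at 6 months and 0.69 at 12 months, taken from the PCARE study (Precision analysis). Assumed, because the article gives neither: the gap between stayers and leavers in the proportion of appropriate services received (0.10, 0.20, 0.30), and the share c of leavers whose charts can be abstracted (0, 50, 75, 100%).

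**1. Reproduce the plan's precision figures.** SE = sqrt(p(1 − p)/30); margin = 1.96 × SE.
- p = 0.78: SE = sqrt(0.78 × 0.22/30) = 0.0756; margin 0.148. The plan states 0.076 and 0.15.
- p = 0.69: SE = sqrt(0.69 × 0.31/30) = 0.0844; margin 0.166. The plan states 0.084 and 0.17.

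Both agree after rounding.

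**2. Patients who could be affected.** 30 × (1 − p).
- 6 months: 30 × 0.22 = 6.6.
- 12 months: 30 × 0.31 = 9.3, which leaves 20.7 with an assessment.

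These are upper figures for the dropout rule, because non-completion also includes missed visits by patients who never left.

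**3. Error of a completers-only mean.** The mean over all enrolled equals the stayers' mean minus (missing share × gap), so the error is missing share × gap.

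| Assumed gap | 6 months (0.22) | 12 months (0.31) |
|---|---|---|
| 0.10 | 0.022 | 0.031 |
| 0.20 | 0.044 | 0.062 |
| 0.30 | 0.066 | 0.093 |

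The mean is too high if stayers receive more services than leavers, and too low if they receive fewer.

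**4. What chart abstraction recovers at 12 months.** With share c of leavers abstracted, and those leavers typical of all leavers, coverage is 0.69 + 0.31c. The remaining error is gap × [0.31 − 0.31c/(0.69 + 0.31c)].

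| c | Patients covered | Gap 0.10 | Gap 0.20 | Gap 0.30 |
|---|---|---|---|---|
| 0% | 20.7 | 0.031 | 0.062 | 0.093 |
| 50% | about 25 | 0.013 | 0.025 | 0.038 |
| 75% | 27.7 | 0.006 | 0.012 | 0.017 |
| 100% | 30 | 0 | 0 | 0 |

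This holds only for the record-based part of the score. The self-report part stays missing for leavers who give no interview.

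**5. Which times are the scheduled ones.** Table 3 puts this measure at baseline, 3 and 6 months; the Phase IV text puts assessments at baseline, 6 and 12 months. They agree only on baseline and 6 months. If Table 3 governs, there is no 12-month preventive-care value and the 6-month column in step 3 is the relevant one.

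**The case against.** **Silence in a journal article.** Whether abstraction continues after withdrawal is usually settled in the full protocol and consent form, which are not shown. This stands against any claim that the plan ends data collection at dropout. A reader might infer that from the rule, but the text neither stops nor continues abstraction. It does not dispose of the point, because the fallback is stated: an earlier assessment becomes the end-of-treatment assessment for every outcome.

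**Leavers are not discarded.** A reader might also infer that the outcome is confined to those who stay. That is too strong. Leavers keep baseline and any earlier assessments, are pursued for a final one, and otherwise have an earlier value used. The missing-data section also has all available measurements contribute and plans sensitivity analysis. How far this reaches preventive care is unclear, since no model is named for it.

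**Consent.** Permission is still to be sought and may not survive withdrawal. This stands, and the fix must depend on it.

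**Feasibility rates.** It is tempting to say that assessment completion and treatment attendance would partly record one event. The article lists them as separate rates and nowhere says that assessments end when visits end. The pairing of study dropout with an end-of-treatment assessment is loose wording and proves no more.

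**Low stakes.** The outcome is exploratory, the primary outcomes are feasibility and acceptability, and the article disclaims efficacy inference. This stands and sets the severity.

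**Conclusion.** The point holds as a cheap improvement of low severity. One dropout rule covers all outcomes and leaves the planned chart access unused for the record-based part of preventive care, so leavers' endpoint values would be early, off-schedule or missing.

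At most about 7 of 30 patients at 6 months and 9 of 30 at 12 months are affected, if completion matches PCARE. The error of 0.03 to 0.09 in a 12-month mean rests on three assumptions: a completers-only analysis, no leaver's chart abstracted, and a gap of 0.10 to 0.30 that the article does not give. Neither the size nor the direction of bias is known, and using an earlier value as the endpoint could bias the result differently. The documents do not support the firm statement that the rule inflates the outcome.

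**What to change.** 1. Reconcile the timing of the preventive-care measure between Table 3 and the Phase IV text.
2. In the missing-data section, state that patients who only stop care-manager visits keep their scheduled assessments.
3. For patients who leave the study, state that chart abstraction continues at the scheduled times unless they withdraw consent to record access, and put that question to them at exit.
4. For the record-based indicators, use the abstracted values in place of the last scheduled assessment.
5. Report a chart-only score beside the combined chart and self-report score.

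The cost is a few sentences in the protocol and consent form, plus research assistant time to abstract charts for at most about 9 patients. The chart-only score will miss services known only from self-report, so it supplements the combined score and does not replace it.

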### Primary analysis

To evaluate feasibility, we will estimate recruitment rate, assessment completion rate, and treatment attendance rate by sample proportions and provide their standard errors based on binomial distribution. We will evaluate acceptability by assessing patient satisfaction (CSQ scores) repeatedly over time (baseline, 6 months, and 12 months). We will analyze improvement in patient satisfaction by a linear mixed-effects model with random subject-specific intercepts to handle correlation between repeated measurements of the outcomes. We will include time as predictor of interest. Significance of improvement in satisfaction over time will be assessed by testing whether the slope of time is zero.

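### The rule for a dropout's end-of-treatment assessment reads as end-point substitution, which the mixed model in the same paragraph does not need and missing at random does not justify

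*Protocol article*

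**What the plan says.** The section Accounting for missing data in the analysis opens with dropouts: reasons are recorded and every effort is made to get a final assessment. It then says: "Failing this, the end-of-treatment assessment will be the patient's last scheduled assessment".

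The same paragraph goes on to a multilevel model with random intercepts for the Client Satisfaction Questionnaire (CSQ), and to PROC MIXED for outcomes with gaps. Of that model it says "Measurement at each time point on each patient contributes to the analysis" and "Thus, complete outcome information for all patients at all sessions is not needed". Validity rests on a stated condition: "The inferences from incomplete data are valid, provided the missing data are missing at random". Where that is doubted, the plan adds a model for the missingness and a sensitivity analysis.

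On timing, Phase IV says "The RA will assess patients at baseline, 6 months, and 12 months". Under Primary analysis, acceptability is judged on the CSQ at those three times: "Significance of improvement in satisfaction over time will be assessed by testing whether the slope of time is zero". For feasibility, the same section says "we will estimate recruitment rate, assessment completion rate, and treatment attendance rate by sample proportions". Exploratory analysis promises average levels and rates with confidence intervals and names no model. Precision analysis takes its expected rates from the earlier trial of the intervention: "PCARE's observed assessment completion was 0.78 at 6 months and 0.69 at 12 months".

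**The concern.** The sentence stands under a heading about missing data in the analysis, so a reader will take it as an analysis rule. With visits at baseline, 6 and 12 months, the record standing in for a missing 12-month assessment can only be the 6-month or the baseline one. An available-data likelihood model has no use for such a record, and missing at random does not justify treating an early value as a late one.

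The article does not say where the stand-in is used. If it enters the CSQ model as a later record, it distorts the time slope, which is the test for acceptability, one of the two primary outcomes. A patient seen only at baseline would then have a baseline score standing as satisfaction at the end of treatment. The exploratory estimates are the most exposed, because no model is named there that would make the stand-in redundant.

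**Working it through.** **Inputs from the article.** N = 30; assessment completion 0.78 at 6 months and 0.69 at 12 months (Precision analysis); visits at 0, 6 and 12 months; random-intercept model with a linear time slope (Primary analysis).

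**The article's own figures.** SE = √(p(1−p)/30), margin = 1.96 × SE.
- p = 0.78: SE 0.0756, margin 0.148 (stated 0.076 and 0.15).
- p = 0.69: SE 0.0844, margin 0.166 (stated 0.084 and 0.17).

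Both reproduce.

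**Patients affected.** Monotone dropout is assumed.
- Complete: 0.69 × 30 = 20.7.
- Lost after 6 months: (0.78 − 0.69) × 30 = 2.7.
- Baseline only: 0.22 × 30 = 6.6.

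So about 9 of 30 lack a 12-month assessment. Filling every missed visit would create 2 × 6.6 + 2.7 = 15.9 records out of 90 that were never observed.

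**Reading A: earlier values fill all missed visits.** Let D be the true 12-month change, the same in everyone, and f the share of it reached by 6 months. With all three visits filled, the slope over 12 months equals the mean of the 12-month minus the baseline value:

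retained share = 0.69 + 0.09 × f + 0.22 × 0

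| f | retained share | attenuation |
|---|---|---|
| 0.25 | 0.7125 | 29% |
| 0.5 (linear) | 0.735 | 26% |
| 0.75 | 0.7575 | 24% |
| 1 | 0.78 | 22% |

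**Check by simulation.** The following settings are assumptions, not figures from the article: linear change of 2 CSQ points over 12 months, between-patient SD 3, residual SD 2, dropout unrelated to outcome, N = 30, 300 runs.

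| Data entering the model | mean 12-month change | mean model SE | SD across runs |
|---|---|---|---|
| Observed records at their own times | 2.01 | 0.60 | 0.64 |
| Earlier values fill all missed visits | 1.48 | 0.46 | 0.51 |

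The filled-in result agrees with 0.735 × 2 = 1.47. Its model SE falls because carried values count as data, and it is below the estimate's own variation across runs (0.46 against 0.51). With a true change of −2 the filled-in estimate was −1.44, so a decline shrinks too.

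**Reading B: the 6-month record of a patient lost after 6 months is relabelled month 12, and nothing else is filled.** Mean 1.90 against 2.0, a bias of about 5%. Baseline-only patients keep their baseline record as baseline.

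**Reading C: each record keeps its actual time.** This is the observed-data row above: no bias.

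**When dropouts fare differently from completers.** Completers gain 2 points.
- Dropouts truly lose 2: true mean 0.69 × 2 − 0.31 × 2 = 0.76. Filling gives 0.69 × 2 + 0.09 × (−1) = 1.29 by formula and 1.35 in simulation; observed data give 1.97.
- Dropouts truly do not change: true mean 0.69 × 2 = 1.38. Filling gives 1.39; observed data give 1.97.

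The direction of the bias therefore depends on how dropouts would have fared. The mixed model on observed data is also wrong in these two cases, since missing at random fails in them.

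**The case against.** The strongest defence is that the sentence only names which visit counts as a dropout's last. It follows an instruction on data collection, speaks of a scheduled assessment rather than a carried value, and is followed at once by a description of a model that uses observed data at each time. On that reading nothing conflicts and nothing is biased. Read literally, the last scheduled assessment could even be the missed 12-month visit itself, which would make the rule empty.

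Much of this stands. A reader might infer that the plan prescribes last observation carried forward and that the two parts of the paragraph cannot both hold. The text supports neither as a certainty: the method is not named, and no section feeds a substituted value into the model. A reader might also infer that the rule always pulls change toward zero; the last two cases in the working show otherwise. Lastly, a reader might infer that substituted assessments count as completed, so that 12-month completion would read 100%. No section says so, and Precision analysis plans on a separate, lower rate of 0.69 at 12 months.

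The study is also a single-group pilot that disclaims efficacy testing, which limits the harm. The defence does not rescue the sentence, however. If it is only a label, it has no function in the analysis and should say so. Its more natural meaning, under that heading, is a stand-in for a missing value.

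**Conclusion.** The point holds as a badly fixed rule, not as proof of a biased analysis. The sentence reads as end-point substitution, does not say where the substitute is used, and is at odds with the available-data method beside it. Its effect ranges from none (actual times kept), through about 5% (relabelling only), to about 26% attenuation with too small a standard error (all missed visits filled). The 26% rests on the article's 0.78 and 0.69, monotone dropout unrelated to outcome, and linear change; other time courses give 22% to 29%. If dropouts deteriorate, improvement can instead be overstated. Because the CSQ slope serves a primary outcome and the exploratory estimates have no named model, the sentence should be corrected before analysis.

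**What to change.** Delete the sentence, or limit it to identifying a dropout's last visit for descriptive purposes. Add that only assessments actually done enter the CSQ mixed model and the exploratory estimates, each at its actual time since baseline, and that no earlier value is used as the 12-month value. The planned sensitivity analysis for data not missing at random should stay, since it addresses dropouts who fare differently.

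For clarity, add that the assessment completion rate counts only assessments actually obtained at each visit. The article does not say otherwise, so this confirms its meaning rather than corrects it.

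The cost is one sentence removed or narrowed and two short ones added, with no new data. The number reported at 12 months will be those actually assessed, about 21 of 30 at the assumed rate.
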